### 2.7. Intervention

#### 2.7.1. Experiment Group: Pharmacopuncture

Since this trial is a pragmatic study that reflects Korean medical clinical practice, in which personalized treatment is provided according to the patient’s clinical status, the types and methods of pharmacopuncture, acupoints, amount of injection, and depth of injection have not been predetermined. Rather, the health practitioners (Korean medicine doctors) will determine the treatment procedure based on the participant’s clinical status. However, in this trial, the types of pharmacopuncture are limited to placental, Hwangryunhaedok-tang, and Bufonis venenum pharmacopuncture; these are already performed at each research institution and are the most commonly used insomnia treatments in a previous survey [36].

For pharmacopuncture, the acupoints GV20, Ex-HN3, Ex-HN22, GB12, HT7, CV4, and CV6, which were used for insomnia treatment in a previous study [41], will be used, but we will allow the Korean medical doctors to change the acupoints used according to their clinical decision based on the patient’s symptoms and condition.

#### 2.7.2. Control Group: Acupuncture

The comparator treatment will be acupuncture, which is the most commonly used method for treating insomnia in Korean medical practice according to a previous survey [31]. Similar to the pharmacopuncture treatment, the health practitioners will decide the acupuncture protocol in terms of the acupuncture type, acupoints, needle type, depth of insertion, and retention time, depending on the patient’s condition.

Nevertheless, based on previous studies on insomnia and consensus between Korean medicine specialists in neuropsychiatry [42,43], we primarily selected the acupoints GV20, EX-HN3, and bilateral HT7, PC6, BL63, and KI4, but we will allow the practitioners to modify the acupoints used according to their clinical decisions. All treatment-related parameters will be recorded for analysis.

Both pharmacopuncture and acupuncture will be performed by Korean medicine doctors with more than 2 years of experience in acupuncture practice. All practitioners will have completed the standard operating procedure training related to pharmachopuncture and acupuncture administration before this trial’s initiation. To improve adherence to the intervention, treatment, and assessment will be performed through reservation, and participants will be notified of the date of their visit in advance via phone. In addition, investigators will check the participants’ concomitant drug changes and adverse events (AEs) at every visit.

### 2.8. Concomitant Treatment

Medications that have been used 4 weeks prior to participation and medications used for other medical conditions (hypertension, diabetes mellitus, hyperlipidemia, and pain) will be allowed. The participants will be allowed to receive medical care for other conditions that do not affect the treatment results during the trial period. All details regarding concomitant treatment will be investigated at every visit and recorded in the medical records and CRFs.

### 2.9. Outcome Measures

#### 2.9.1. Primary Outcome

The primary outcome measure will be the mean difference in the total Pittsburgh Sleep Quality Index (PSQI) scores pre- and post-intervention (between visits 1 and 11) between the two groups. The PSQI is the most commonly used self-report questionnaire to assess sleep quality and disturbances over the past month. It comprises 19 self-rated items and evaluates seven components: subjective sleep quality, sleep latency, sleep duration, habitual sleep efficiency, sleep disturbances, use of sleep medication, and daytime dysfunction. The total PSQI score ranges from 0 to 21, with higher scores indicating poorer sleep quality [44]. The PSQI score will be assessed at baseline, visit 6, post-intervention, and follow-up visits.

#### 2.9.2. Secondary Outcomes

The secondary outcomes will be changes in the ISI, PSQI, and visual analog scale (VAS) scores of subjective symptoms accompanying insomnia, and the difference in quantity and quality of sleep recorded using a sleep diary and actigraphy during the trial period. The ISI and VAS scores of subjective symptoms accompanying insomnia, sleep diaries, and actigraphy will be checked at the baseline, visit 6, post-intervention, and follow-up visits. In addition, changes in scores on the Core Seven-Emotions Inventory Short Form (CSEI-S), Pattern Identification Tool-Insomnia (PIT-Insomnia), and body composition test between the pre- and post-treatment periods will be analyzed. The ISI is a self-report questionnaire designed to assess a patient’s subjective perception of insomnia severity. It consists of seven items rated on a 5-point Likert scale. The total ISI score ranges from 0 to 28 [45], with a higher score indicating more severe insomnia; the cutoff point for clinically significant insomnia is 15 [46].

We will assess the improvement in physical symptoms accompanying insomnia, such as headache, dyspepsia, and fatigue, using the VAS scale.

The PIT-insomnia, developed by Lee et al. [47] is a self-report questionnaire for assessing the pattern identification of insomnia.

The CSEI-S is a self-rating questionnaire used to assess the quantity of seven basic human emotions: joy, anger, thought, depression, sorrow, fear, and fright, based on the seven emotions theory in Korean medicine [48].

A sleep diary is a useful tool for obtaining sleep-related information and monitoring the treatment progress [49]. Eligible participants will be asked to complete a sleep diary after waking up daily. The sleep diary items included bedtime, waking time, sleep onset latency, sleep duration, number of awakenings, use of medications, and sleep satisfaction scores ranging from 0 to 100, with higher scores indicating greater sleep satisfaction.

The eligible participants will be asked to place an actigraphy device (ActiGraph wGT3X-BT; MTI Health Services Company, Pensacola, FL, USA) on their non-dominant wrists to obtain objective sleep-related information. Records from the actigraphy device at baseline, visit 6, post-intervention, and follow-up visits will be downloaded and saved. The extracted sleep-related variables will be used to compare the changes between the groups and their consistency with sleep diary records.

We will calculate the total time in bed from the sleeping time and waking time recorded in the sleep diary. The sleep diary assesses the sleep onset latency and total sleep time. We will also calculate sleep efficiency from the items entered in the sleep diary. Additionally, we will analyze objective sleep-related data such as sleep onset latency, total sleep time, and sleep efficiency based on actigraphy findings.

Body composition of the participants will be measured using the InBody S-10 (Biospace, Seoul, Republic of Korea) at baseline and post-intervention visits. We will compare the changes in body weight, skeletal muscle mass, body fat mass, body mass index, visceral fat area, and extracellular space between the two groups.

#### 2.9.3. Quality of Life Assessment

Quality of life will be measured at the baseline, post-intervention, and follow-up visits using the 5-level EuroQoL-5 dimension [50], the EuroQol-visual analog scale [51], the 36-Item Short Form Health Survey [52], and The Korean Health-Related Quality of Life Instrument with eight items [53].

#### 2.9.4. Cost Data

In this study, direct medical and non-medical costs and costs of productivity loss will be considered. Direct medical costs include expenses associated with pharmacopuncture, prescribed hypnotics, first or revisit diagnoses, and examination costs. Direct non-medical cost consists of the round-trip expenses for participating in clinical trials. The productivity loss costs will be calculated by multiplying the lost productivity scores by the hourly wage. The Work Productivity and Activity Impairment (WPAI) questionnaire will be used to calculate the lost productivity scores [54]. 

The result of the cost-effectiveness analysis will be expressed as the incremental cost-effectiveness ratio (ICER). This economic evaluation will include all types of costs and consider the quality-adjusted life-years (QALY) for effectiveness. QALY will be calculated using the EQ-5D-5L, and gross domestic product (GDP) per capita will be used as the threshold value for willingness to pay.

#### 2.9.5. Additional Evaluation

To explore the effects of the interventions on sleep parameters, including sleep architecture and sleep-related hormones, 15 participants per group enrolled at Pusan National University Korean Medicine Hospital, where polysomnography referral is available, will undergo polysomnography and saliva study of melatonin and cortisol before the start and after termination of the treatment. We will assess sleep architecture (total sleep time, sleep efficiency, sleep latency, proportions [%] of non-rapid eye movement sleep [N1, N2, N3], rapid eye movement, and arousal index), respiratory events (apnea-hypopnea index, respiratory disturbance index, respiratory arousal index), periodic limb movement index, periodic limb arousal movement, and parasomnia events using polysomnography.

#### 2.9.6. Safety Assessment

To assess safety, laboratory and electrocardiography tests will be conducted during the screening and post-intervention visits.

Investigators interviewed and recorded all AEs based on the symptoms reported by the participants at every visit during the trial period. AE severity will be graded using Spilker’s three-level criteria: mid, moderate, and severe. The causality of AEs will be rated as definitely related, probably related, possibly related, probably unrelated, definitely unrelated, or unknown based on the World Health Organization-Upsala Monitoring Centre causality assessment system.

All reported AEs and laboratory abnormalities during the trial period will be collected, and the frequency and percentage of participants who identified AEs or laboratory abnormalities in both groups will be calculated. The incidence of AEs will be compared between the two groups.

### 2.10. Data Collection and Management

To promote retention and complete follow-up, we will be in regular contact with the participants. The participants will be able to contact the researchers and obtain the information they need at any time, as contact information will be provided. Trained clinical research coordinators will record the data collected in the CRF. We will utilize electronic CRF (e-CRF) using the Internet-based clinical trial management public platform provided by the National Institute for Korean Medicine Development. To ensure the accuracy and quality of this clinical trial, all members of the research team will be educated on the standard operation procedure, including writing the CRF, data entry, and study procedures. For data quality management, the data value range for each measurement item will be set in advance. If the entered data values are outside the preset range, data queries will be issued. Only the investigator in charge of the data management will be able to access the data entered into the e-CRF. After study completion, the data will be stored for 3 years as per the relevant laws.

### 2.11. Data Monitoring and Auditing

Data monitoring will be conducted to protect the participants’ rights, ensure adherence to the study protocol, and ensure the completeness of the collected data. The Clinical Research Center of the Korea Institute of Oriental Medicine, which has no competing interests of this trial, is responsible for the data monitoring. Monitoring will be conducted by examining the consistency of the CRF and the source documents and by reviewing the safety data of the participants, including laboratory tests and AEs. Routine monitoring visits at each site will be scheduled, and additional visits will be conducted, depending on the recruitment status. If unexpected and serious AEs are associated with the intervention in this study, the Clinical Research Center of the Korea Institute of Oriental Medicine will have access to the interim results to advise on trial discontinuation. The principal investigator will make a final decision to terminate the trial.

Auditing will be performed periodically at each research institution by the Clinical Research Center of the Korea Institute of Oriental Medicine, independent of this study.

### 2.12. Criteria for Discontinuation and Withdrawal

Treatment will be discontinued and participation will be withdrawn according to the following criteria: (1) Request for discontinuation or withdrawal of consent by participants or their legal representative; (2) diagnosis of any medical condition that makes the participant ineligible for this trial; (3) incidence of any serious AEs; (4) violation of the study protocol; (5) changes in dosage or type of sleeping pills already used during the trial period (from screening test to post intervention); (6) loss to follow-up; (7) use of any medications or undergoing therapies that will affect the study results without the permission of investigators; (8) more than three consecutive absences from intervention or participation in less than seven sessions of the intervention; and (9) other conditions wherein participation is judged to be inappropriate by the investigator in charge.

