### 2.13. Statistical Analysis

Continuous variables will be presented as means and standard deviations, while categorical variables will be presented as frequencies (%) and percentiles. The homogeneity of the demographic characteristics and baseline variables between the two groups will be evaluated to choose the appropriate analysis methods. The independent t-test or Mann–Whitney U-test will be used for analysis, depending on the normality of data distribution. If there were significant between-group differences in baseline variables or demographic characteristics, regression analysis with covariates (analysis of covariance) will be conducted. The primary and secondary outcome measures will be analyzed in the same manner. We will also examine the consistency between objective and subjective sleep-related data obtained from actigraphy and patient-reported questionnaires.

Additionally, we will analyze the changes in sleep parameters assessed using polysomnography and sleep-related hormones before and after treatment in participants who underwent polysomnography. Both the full analysis set (FAS) and per-protocol analyses will be conducted. The FAS is the primary analysis of effectiveness and safety. It will include all participants initially assigned to each group, except those who did not meet the eligibility criteria, those who had not received any intervention, or those who had not completed any outcome measurements. The per-protocol analysis will include participants who have completed more than seven sessions. All statistical analyses will be performed by an independent statistical expert blinded to the allocation and procedure using SPSS version 25 (IBM, Chicago, IL, USA). Statistical significance is set at *p* < 0.05.

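### Section 2.12 ends trial participation along with treatment, so the V11 PSQI is lost after events that may depend on response, and the primary comparison is exposed to bias of unknown size and direction

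*Protocol article*

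**What the plan says.** In the protocol article, one sentence in section 2.12 governs all nine criteria: "Treatment will be discontinued and participation will be withdrawn according to the following criteria". Among them are:

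- criterion 3, any serious adverse event;
- criterion 4, "violation of the study protocol", with no qualifier;
- criterion 5, "changes in dosage or type of sleeping pills already used during the trial period (from screening test to post intervention";
- criterion 7, "use of any medications or undergoing therapies that will affect the study results without the permission of investigators";
- criterion 8, "more than three consecutive absences from intervention or participation in less than seven sessions of the intervention".

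No section provides for assessing a participant after withdrawal. Section 2.10 describes regular contact to support retention, but does not extend it to people whose participation has been ended.

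Section 2.9.1 makes the primary outcome the between-group difference in PSQI change from V1 to V11. PSQI is also taken at V6 and V12. Its seven components include "habitual sleep efficiency, sleep disturbances, use of sleep medication, and daytime dysfunction". Section 2.13 compares the groups by t-test or Mann–Whitney test, with covariate adjustment if baselines differ. The primary set is the full analysis set (FAS), which takes everyone assigned "except those who did not meet the eligibility criteria, those who had not received any intervention, or those who had not completed any outcome measurements". For the supporting set, "The per-protocol analysis will include participants who have completed more than seven sessions". Sections 1 and 3 present the trial as pragmatic, and section 3 says it should inform clinical and policy decisions.

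**The concern.** Stopping study treatment and stopping outcome collection are different decisions, and section 2.12 joins them. The listed events happen after randomisation and may be linked to how the participant is sleeping. Someone may cut pills because sleep has improved, raise them because it has not, or stop attending because the treatment is not helping. Pill use is also scored within the PSQI, so criterion 5 removes people for a change in something the primary outcome measures. Section 2.6 says that participants and practitioners cannot be blinded, so these behaviours can differ between arms.

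Two things are at stake. First, the primary result would describe people who attended and kept their existing medication stable, whereas a pragmatic trial compares assigned strategies. Second, if withdrawal differs by arm, the retained groups are no longer the groups that randomisation made comparable. Agreement between the FAS and per-protocol results would then reassure less than it seems to, because the two rest on largely the same V11 values.

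**Working it through.** **Who has a V11 PSQI if section 2.12 is applied as written**

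| Participant | V11 PSQI | In FAS as defined | In per-protocol set |
|---|---|---|---|
| 0 sessions | no | no (untreated) | no |
| 1 to 6 sessions | no (criterion 8) | yes, if any outcome was measured | no |
| exactly 7 sessions | yes | yes | no |
| 8 to 10 sessions | yes | yes | yes |
| existing pills changed before V11 | no (criterion 5) | yes, if any outcome was measured | not named in the definition |

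By session count, the FAS members with a V11 value differ from the per-protocol set only in those with exactly seven sessions. In respect of pill changes, the V11-evaluable group is narrower than the per-protocol definition requires.

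**The plan's own figures (section 2.3)**

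- Planned changes are 6.9 (SD 2.51) and 4.93 (SD 2.70), a difference of 6.9 − 4.93 = 1.97.
- The common SD is √((2.51² + 2.70²)/2) ≈ 2.61, so the standardised difference is about 0.756. The stated effect size of 0.92 does not follow from these inputs; that is a separate matter and is not used here.
- With 0.756, 95% power, two-sided 0.05, 2:1 allocation and a Mann–Whitney test, the requirement is 74 and 37, as stated.
- Dropout: 74/0.8 = 92.5 and 37/0.8 = 46.25, against the stated 92 and 46. A 20% loss of 138 is 27.6 people.
- Power is about 95% to 96% with 74/37 and about 98% with 92/46. The 20% allowance therefore covers the loss of numbers; what remains is selection.

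**Size of the selection effect**

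Let q be the fraction withdrawn in an arm and D the mean improvement of the retained minus that of the withdrawn. The arm mean is (1 − q) × retained + q × withdrawn, so the retained mean exceeds it by q × D. With the same D in both arms, the bias in the difference (pharmacopuncture minus acupuncture) is (q_P − q_A) × D. The documents give neither q by arm nor D. Assume D = 2.6 points, about one SD:

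- 10% v 20%: (0.10 − 0.20) × 2.6 = −0.26 points;
- 10% v 25%: (0.10 − 0.25) × 2.6 = −0.39 points, and 0.39/1.97 = 20% of the planned difference;
- the same rates with the arms exchanged: +0.26 and +0.39 points;
- equal rates: zero.

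The sign also reverses if those withdrawn are mainly people doing well, for example those cutting pills, because D is then negative.

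**Simulation check** (4,000 runs per scenario, 92/46, SD 2.6, t-test; assumed log-odds of withdrawal rising by 1 or 2 per SD of poorer response within each arm)

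| Withdrawn, pharmacopuncture v acupuncture | Bias (points) | Rejection rate when true difference is 0 |
|---|---|---|
| 20% v 20% | about 0 | 5% to 6% |
| 15% v 30% | −0.31 to −0.45 | 10% to 14% |
| 10% v 40% | −0.62 to −0.89 | 19% to 39% |

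All three scenarios average 20% withdrawal overall, the plan's own dropout figure. The 10% v 40% row is an extreme case.

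**The case against.** The strongest reply is that the FAS does not exclude withdrawn participants. Anyone treated and measured at least once, for example at V6, stays in it, and how a missing V11 value is handled belongs in a statistical analysis plan that is not shown. The first part stands: a reader might infer that the FAS itself shrinks to the per-protocol set, and section 2.13 does not say so. Only its V11-evaluable part shrinks. The second part does not remove the concern, because imputation can only model outcomes that the protocol has stopped collecting.

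A reader might also infer that the primary comparison is biased as a matter of fact. The documents do not support that. They give no withdrawal rates by arm, the 20% also has to cover consent withdrawal and loss to follow-up, and equal rates with equal selection give about zero bias.

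Criterion 5 reaches only pills already in use. A participant who starts a pill falls under criterion 7, and only without the investigator's permission, so not everyone with a V11 value will have unchanged medication. The share using pills at baseline is not stated, and stable medication is a deliberate feature of the eligibility rules. These points limit the reach of the concern but do not answer it.

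Finally, the two session thresholds might be read as contradicting each other. They do not: someone with exactly seven sessions stays in the trial and the FAS but falls outside the stricter per-protocol set. The other FAS exclusions are openly declared and are not part of this point.

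**Conclusion.** The concern holds as a risk created by an explicit rule. As written, section 2.12 stops collection of the primary outcome after events that may be related to response, and nothing elsewhere in the article restores it. Even with balanced withdrawal, the V11 result would describe mainly adherent participants with stable existing medication, which does not match the pragmatic aim.

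Bias in the between-group difference depends on unequal withdrawal or unequal selection. Under the assumed 2.6-point gap and 10% v 20% to 25% withdrawal it is about 0.26 to 0.39 points, in either direction. These are illustrations; the documents determine neither the size nor the sign. It deserves correction because outcomes not collected cannot be recovered at analysis.

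**What to change.** Leave the treatment-stopping criteria in section 2.12 unchanged, but state separately what ends study treatment and what ends trial participation. Continue the scheduled V11 and V12 assessments for every randomised participant who can be reached and has not withdrawn consent to data collection. Analyse them in their allocated group whatever their pill changes or attendance, recording those events, and keep the per-protocol set as supportive. The session thresholds need no alignment.

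The cost is a protocol amendment with matching analysis wording; the visits are already scheduled. Section 2.16 says the trial is under way, so participants already withdrawn stay unmeasured unless they can be re-contacted, and follow-up will differ before and after the amendment. That should be reported. Those lost to follow-up will still be missing. Including less adherent participants may dilute the contrast somewhat, but that is part of the effect a pragmatic trial sets out to estimate.
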